## **ABSTRACT OF THE PROJECT (Max. 200 words)**

A growing body of evidence suggests that high-intensity interval training (HIIT) improves aerobic fitness and body composition that are similar to or better than training endurance training eg. moderate-to-vigorous intensity training (MVCT) despite a lower training time commitment. However, for sedentary individuals, the strategy that HIIT as an alternative to traditional continues exercise has been argued because it is extremely hard. Although it has been reported that HIIT seems more enjoyable than MVCT, such findings were from young active men or normal weight individuals. Whether HIIT results in superior improvements in cardiorespiratory fitness and metabolic indicators when compared with MVCT in obese individuals warrant further investigation. In terms of the study designs for comparing fat loss between HIIT and MVCT, there are common flaws including lacking quantitative estimation of energy expenditure and neglecting the effects of additional physical activities besides the exercise training program. Thus, whether short-term HIIT training is superior to MVCT for improving body composition in overweight and obese individuals has not been fully supported. In addition, overweight and obesity may affect women's health with irregular menstrual cycle and abnormal sex hormones, thus it is necessary to examine whether HIIT has influences on sex steroid hormones in sedentary overweight young women.

## **PROJECT DETAILS**

### **Objectives**

Using a less demanding HIIT protocol with 60 repetitions of 8s/12s work-rest intervals at a lower resistance for 4 days/week, the purpose of this study was to compare the effects of 5-week HIIT and MVCT interventions on cardio-metabolic health outcomes, sex hormones levels and physical activity enjoyment scale (PAES) in overweight female subjects.

### **Background of the Project**

Overweight and obesity, associated with a number of comorbidities and metabolic disorder, has become a serious public health problem worldwide. Weight reduction improves cardiorespiratory fitness and lowers metabolic risk factors [Garber et al, 2011]. Although weight increase occurs for all ages in both developed and developing countries, such increase is the most rapid for people between 20 and 40 years old [Ng et al, 2014].

The recommended exercise prescription for most adults is typically a regular moderate-intensity continuous exercise program for a total of over than 150 min·wk to improve and maintain physical fitness and health [Garber et al, 2011]. However, the inactive nature of sedentary individuals and the “lack of time” excuse tend to prevent people from being engaged in regular physical activity [Hardcastle et al, 2013].

An increasing amount of evidence indicates that high-intensity interval exercise (HIIT) has the potential to improve cardiorespiratory fitness, thus reducing obesity and the associated comorbidities [Trapp et al, 2008; Perry et al, 2008]. However, although previous studies have reported that 2-week HIIT protocol resulted in marked

increments in  $\dot{V}O_{2\max}$  by 9% to 13%, the improvement of cardiorespiratory fitness as a result of HIIT did not always happen in 2 to 6 weeks of HIIT training [Iaia et al, 2009; Astorino et al, 2011; Allemeier et al, 1994]. At present, in the studies that compared continuous exercise with HIIT, not a few have observed the physiological differences between MVCT training around 150 minutes per week and HIIT training.

Overweight and obesity may affect women's health with irregular menstrual cycle and abnormal sex hormone levels [Kulie et al, 2011], as high levels of androgen and estradiol are observed in obese young women [Tchernof & Despres, 2000]. Sex steroids hormones are associated with the regulation of body fat distribution in both men and women [Tchernof & Despres, 2000], therefore, sex steroid hormones may play a supportive role in changes of body weight. However, to our knowledge, no researches have reported whether HIIT training has influences on sex hormones in sedentary overweight young women.

It has been reported that training with 8s/12s work-rest intervals in 20 minutes for 15 weeks improved body fat distribution and insulin resistance of young women, when compared to 40 min of steady-state exercise with the similar energy expenditure as HIIT [Trapp et al, 2008]. Given that the study designs for comparing fat loss between HIIT and MVCT has the common flaws, such as the lack quantitative estimation of energy expenditure [Lunt et al, 2014], and neglecting the effects of additional physical activities of the participants besides the implemented exercise training program [Trapp et al, 2014]. Thus, whether short-term HIIT training is superior to MVCT for weight loss and body fatness reduction in overweight and obese individuals has not been fully supported.

Recently, there has been the argument against the use of HIIT as an alternative to

traditional continuous exercise, because HIIT training is extremely hard; as a result, it is likely to be a deterrent for the largely sedentary/obese population [Ekkekakis et al, 2011; Hardcastle et al, 2013]. Enjoyment is an important factor for long-term adherence. Although it has been reported that HIIT seems more enjoyable than either MVCT [Bartlett et al, 2011] or continuous vigorous-intensity exercise [Jung et al, 2014], such findings were from young active men [Bartlett et al, 2011] or normal weight individuals [Jung et al, 2014]. Because of these considerations, the claim that low-volume HIIT training is more enjoyable than MVCT training needs to be examined further in different populations.

Based on the above knowledge, it is hypothesized that: 1) both HIIT and MVCT would induce improvements in cardio-metabolic parameters including  $\dot{V}O_{2max}$ , body weight and fat, blood lipids, and sexual hormones, 2) the time-efficient HIIT would be a more enjoyable exercise mode in comparison with MVCT.

## **Research Methodology and Implementation Plan**

### **Participants**

A public notice including the research purpose, qualifying criteria, research process, matters need attention and privacy protection will be released to the participants who are interested in this study. The inclusion criteria for the subjects are as follows: (1) between 18 and 30 years old; (2) sedentary as defined by reporting less than 60 minutes exercise every week in the previous 6 months; (3) body fatness over than 30% measured by a 5-serial of frequent bioimpedance analyzer (Biospace Inbody 720, South Korea), and (4) a doctor certificate approving the practice of vigorous exercise. Each volunteer needs to complete a PAR-Q form and a menstrual cycle survey prior to being admitted into the study. The subjects who have any barriers to

physical activity, smokers, alcoholics, and contraceptive or prescribed drug users will be excluded.

With a power of 0.8 at  $\alpha=0.05$ , an assumed correlation of 0.8 between pre-treatment and post-treatment, the sample size for HIIT group is estimated to be 12. When a dropout rate of 20% is allowed, a total sample size of 30 subjects is needed. 30-36 qualified sedentary overweight young females will be recruited. All subjects should provide written informed consent before participation. The subjects will be randomly assigned to either HIIT or MVCT group. By the end of the study, 80% subjects are expected to complete the experiment (Fig 1).

[figure not shown]

**Fig 1** Manipulation Route

### Experimental protocol

The experimental protocol consists of pre- and post-training measurements and a 5-week HIIT or MVCT intervention. Measures of  $\dot{V}O_{2max}$ , body composition and blood assays be taken in pre- and post-training measurements. Baseline measures will be

taken within 3-7 days before the 5-week exercise intervention, and post-training measures will be taken 3-7 days following the last training session. All pre- and post-training testing sessions will be arranged in the follicular or late luteal phase of each subject according to the self-reported menstrual cycle survey. During test and training sessions, the same verbal encouragements will be given by the same helpers.

### **Exercise training intervention**

The HIIT cycling protocol is from a previous study done by Trapp et al. (2008). After a 3-min warm-up at 50 W, each participant will conduct 8 s of sprinting and 12 s of passive rest for a maximum of 60 repetitions on an ergometer. The initial resistance is 0.5 kg and the resistance will be increased by 0.5 kg once an individual can complete two consecutive 20-min intermittent sprinting exercise sessions at the given workload. Subjects will have a cool down for 3 min at 50 W followed by standard stretches. Heart rate, ratings of perceived exertion (RPE) and training power will be recorded before and after every five sprints. Enjoyment of exercise will be assessed by PAES scale [Kendzierski & DeCarlo, 1991] immediately after every training session. When an individual misses a session, she should make it up later in order to complete 20 HIIT sessions within 5 weeks. To estimate exercise intensity and energy output,  $\dot{V}O_2$  measures during the first and last training session will be taken for all the subjects in HIIT group.

For MVCT training [Trapp et al, 2008], each subject starts a 3-min warm-up at 50 W, and then exercises at an initial workload of 60%  $\dot{V}O_{2max}$  of the pre-training test for 40 min with a rhythm at 60 rpm. After every training session, a 3-min cool-down and stretching will be conducted. Once an individual can complete two consecutive exercise sessions at the specified level of exercise strength, resistance will be

increased by 0.5 kg until the workload being reached the level of 80%  $\dot{V}O_{2\max}$  of the pre-training test. HR, RPE and training power will be recorded every 5 min during the exercise training, PAES scores will be assessed in the same way as for the HIIT group.

## **Measures**

### *Body composition*

Height and weight will be measured by using standard conventional methods with light clothing. Body mass index (BMI) was calculated by weight and height. Body composition will be assessed after baseline blood sampling and 3 days following the last training session.

### *$\dot{V}O_{2\max}$ test*

$\dot{V}O_{2\max}$  will be performed at baseline and at least 3 days following the last training session. After a 2 min cycling warm-up at 30 W, graded exercise test will start at the initial workload of 50 W and increased by 25 W every 3 min till completion. Subjects will be asked to maintain a cycling speed of 60 rpm unless reaching the criteria or volitional exhaustion.  $\dot{V}O_{2\max}$  will be assessed by a calibrated breath-by-breath analysis system (Meta-Max 3B, Cortex Biophysik GmbH, Leipzig, Germany). The test will be terminated when the subjects meet any two of the following criteria: (1)  $\dot{V}O_2$  reached a plateau with a change less than 150 mL·min, (2) heart rate reached age-predicted maximal level (220-age), (3) respiratory exchange ratio (RER)  $\geq 1.10$ , and (4) rating of perceived exertion (Borg's) scale reached. A 5-min recovery at 30 W will be carried out followed by the test.

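### The VO2max test can be stopped by criteria that do not include a VO2 plateau, so the recorded value may understate VO2max

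*Protocol*

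**What the plan says.** The VO2max test section of the protocol describes a graded cycle test starting at 50 W, with the load "increased by 25 W every 3 min till completion". Women keep to 60 rpm "unless reaching the criteria or volitional exhaustion". The section then states: "The test will be terminated when the subjects meet any two of the following criteria". The four criteria are:

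1. VO2 "reached a plateau with a change less than 150" mL/min
2. heart rate at 220 minus age
3. RER of at least 1.10
4. "rating of perceived exertion (Borg's) scale reached", with no level given in the available text (it may have been lost in conversion from the PDF)

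The section describes no verification bout and no rule to continue until VO2 levels off.

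The result is used in three places. Hypothesis 1, at the end of the background, names VO2max first among the parameters expected to improve. The Experimental protocol section names it first among the pre- and post-training measures. The Exercise training intervention section starts MVCT at 60% of the pre-training VO2max and lets it progress to 80%. HIIT resistance starts at 0.5 kg and rises in 0.5 kg steps, without reference to the test. The Statistical analysis section tests pre/post values within groups, and compares both the change and the percentage change between groups.

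**The concern.** Heart rate, RER and perceived exertion are indirect signs of maximal effort. Used after a test, they help the reader decide whether the effort was maximal. Used to end a test, they fix the recorded value themselves, because VO2 is read at the point where two thresholds happened to be crossed and not where it stopped rising.

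Three things are at stake. The first is the recorded level of VO2max at each visit, which may be too low. The second is the pre/post change. The criteria that end the test are quantities that training may alter, so the two tests could stop at different fractions of the true maximum. The third concerns one group only: an understated baseline would make the true intensity of the MVCT workload lower than its nominal percentage, and the HIIT load would be unaffected.

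**Working it through.** The protocol gives no figure for this point that could be reproduced. The check rests on the logic of the rule and a little algebra.

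**Step 1: which pairs can end a test.** The inputs are the four criteria in the VO2max test section. The number of pairs is 4 × 3 / 2 = 6.

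| Pair | Contains a plateau? |
|---|---|
| Plateau + heart rate | yes |
| Plateau + RER | yes |
| Plateau + exertion | yes |
| Heart rate + RER | no |
| Heart rate + exertion | no |
| RER + exertion | no |

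Three of the six pairs can end a test without a plateau. Heart rate + RER has both thresholds stated, so the point does not depend on the missing exertion level.

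**Step 2: are the criteria stopping rules or later checks?** Two sentences bear on this. One says the test is terminated when two criteria are met. The other makes the criteria an alternative to volitional exhaustion ("unless reaching the criteria or volitional exhaustion"). They agree: a woman who meets two criteria stops, whether or not she could go on.

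**Step 3: how strict is the heart-rate threshold?** For the eligible ages of 18 to 30 it is 220 − 30 = 190 to 220 − 18 = 202 beats/min. This is the full predicted maximum and not a percentage of it. It is still a prediction from age and not the woman's own measured maximum.

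**Step 4: effect on the pre/post change.** Let P0 and P1 be the true maxima before and after training, and f0 and f1 the fractions of them reached when the tests stop (each at most 1).

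- Recorded change = f1·P1 − f0·P0.
- Recorded ratio = (f1/f0) × (P1/P0).

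If f1 = f0, the percentage change is correct and the absolute change is scaled by that common fraction. If the shortfall in mL/min is the same at both visits, it cancels from the absolute change. The percentage change is distorted by the rule whenever f1 differs from f0. It is overstated if f1 > f0 and understated if f1 < f0. The protocol gives nothing from which f0 or f1 could be found.

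**Step 5: effect on the MVCT workload.** If the baseline is understated by a proportion u, a nominal 60% to 80% corresponds to 60(1 − u)% to 80(1 − u)% of the true maximum. As an illustration only, u = 10% gives 0.60 × 0.90 = 54% and 0.80 × 0.90 = 72%. With u = 0 it stays at 60% to 80%. The value of u is an assumption and is not in the documents.

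**The case against.** The strongest reply is that the rule is less damaging than it looks. The heart-rate threshold is the full predicted maximum, and heart rate + RER also requires an RER of at least 1.10. The two exertion pairs cannot be assessed without the missing level. Many tests may end at exhaustion or with a plateau, and the same rule applies to both randomised groups at both visits. All of this stands. It limits how often truncation may occur, but does not remove the three pairs that allow it.

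Four stronger readings are tempting, and the documents do not support them.

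- **At least 150 mL/min is lost.** A reader might infer this from the plateau definition. But the lack of a plateau at the moment of stopping describes the rise already made, not the next one. The next stage could itself be the plateau, or the woman might be exhausted before completing it. The protocol also gives no interval over which the 150 mL/min applies. The loss can be anything from zero upward.
- **The loss is as large as the expected training gain.** The background cites gains of 9% to 13%, but from 2-week HIIT protocols in other studies and not as this trial's expected effect. A loss in one test is also not the bias in a change, which depends on the difference between the two tests (step 4).
- **The gain is inflated.** Lower heart rate, RER or exertion at a fixed load is also what a genuinely higher VO2max would produce. Bias in the percentage gain needs a shift at the same fraction of maximum, and the protocol does not address this.
- **The HIIT versus MVCT contrast is biased.** That would require the two programmes to shift these responses differently. It is possible but not shown.

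Nor do the two sentences on ending the test conflict. They say the same thing, so both need amending.

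**Conclusion.** The point holds as a measurement weakness fixed in the protocol. Three of the six criterion pairs can end the test without a VO2 plateau, so VO2max may be understated in some women. That much follows from the text alone.

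Two consequences are conditional. The measured pre/post change may be distorted if training changes heart rate, RER or perceived exertion at a given fraction of maximum. The true MVCT intensity would fall below its nominal 60% to 80% if the baseline is understated, with no matching effect on the HIIT load. The documents give no basis for the frequency or size of truncation, the direction of any distortion in the change, or a difference between groups. The 54% to 72% figure illustrates an assumed 10% understatement and is not an estimate.

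VO2max is the first-named outcome, not a declared primary one. The change is worth making because it is cheap and removes an avoidable source of measurement error.

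**What to change.** Amend both sentences in the VO2max test section so that the listed criteria are applied after the test, to verify maximal effort, and do not end it. State the perceived-exertion level if it is absent from the source document. For every test, record why it ended and whether a plateau was seen. Report values without a plateau as VO2peak.

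Stopping for safety should be kept separate from these criteria and is for the investigators to define.

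A sensitivity analysis restricted to women whose two tests ended for the same reason is not recommended. It selects on an event after randomisation, among about 24 expected completers (80% of 30), so it would lose the randomised comparison and carry little information.

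The cost is a change of wording and two recorded items per test. The downside is that some tests will run slightly longer.

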### *Blood lipids and sexual hormones*

Blood samples will be taken from the cubital veins at pre- and post-training after a minimum of a 12 h overnight fast. After being clotted for 1 hour at room

temperature, the samples will be centrifuged at 3000 rpm for 10 min and then serum samples will be prepared and stored at a low-temperature refrigerator. High-density lipoprotein cholesterol (HDL-C), low-density lipoprotein cholesterol (LDL-C), total cholesterol (TC) and total triglyceride (TG) and sexual hormones including testosterone and estradiol will be analyzed in the same assay.

#### *Diet and extra physical activity*

Subjects will be instructed to maintain their normal diet and normal daily physical activities throughout the intervention. Food intake data will be recorded by using a 3-day diet recall protocol (two weekdays and one weekend day) during three weeks: one week before the intervention, the third week of the intervention, and the last week of the intervention. Energy intake and diet components will be analyzed by nutrition analysis and management system (Sports Nutrition Research Center, National Institute of Sports Medicine, China). Daily physical activities will be monitored by wearing a pedometer (Yamax SW-200 digiwalker, Japan) on three days in a week (two weekdays and one weekend day) in every week during the 5-week training period.

#### **Statistical analysis**

A two-way mixed analysis of variance (ANOVA) with repeated measures will be used to test the main effect (i.e., group effect) and the interaction effect (time and group interaction) on the outcome variables. For within-group change from pre- and post-values of the relevant outcome variables of interest, paired-sample *t*-test will be performed to test the difference in pre- and post-measures. Change between the pre- and post-measures will be calculated for each outcome variable of interest. Independent-sample *t*-test will be performed to determine the differences of the change and of the percentage change between the two groups. Pearson-product

moment correlation coefficients will be conducted to examine the relationships between the cardio-metabolic health outcomes and sexual hormones.

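### Pre/post outcomes get four overlapping between-group tests with no ranking; one of them, the ANOVA group main effect, estimates only half the training difference, and a single baseline-adjusted test would be better

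*Protocol*

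**What the plan says.** The protocol's Statistical analysis section names a two-way mixed ANOVA that "will be used to test the main effect (i.e., group effect) and the interaction effect (time and group interaction) on the outcome variables". It then adds paired t-tests within each arm, and independent t-tests to "determine the differences of the change and of the percentage change between the two groups". For one between-group question this gives four results per outcome: group main effect, interaction, raw change and percentage change. The section does not rank them and plans no baseline-adjusted comparison.

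Under Experimental protocol, VO2max, "body composition and blood assays be taken in pre- and post-training measurements", that is, once before and once after training. Under Participants, "The subjects will be randomly assigned to either HIIT or MVCT group". The sample-size statement there assumes "an assumed correlation of 0.8 between pre-treatment and post-treatment" and concludes that "the sample size for HIIT group is estimated to be 12".

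The enjoyment scale (PAES) is different. Under Exercise training intervention it is scored at the end of each session, so it has no value from before training.

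**The concern.** With two time points, the ANOVA group main effect compares the arms on the average of the pre and post values. The pre value is taken before any training and cannot carry a training effect. The contrast is therefore half the training difference, plus whatever chance difference the arms had at baseline. It does not answer the trial's comparative question, yet the section lists it as a test of the outcome variables.

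Two consequences follow. A null group effect could be read as no difference between the training modes when the test had little chance of finding one. And because no test is designated, a positive result on any of them could be reported as the finding. Raw and percentage change can also disagree, and the plan does not say which would prevail.

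**Working it through.** **Inputs from the protocol (Participants):** power 0.8, alpha 0.05, pre/post correlation r = 0.8, 12 in the HIIT group, 20% dropout, total 30.

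**Assumptions:** two-sided alpha, 1:1 allocation, equal SD before and after training (set to 1), bivariate normal data, 12 completers per arm.

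**The plan's own figure.** Two arms of 12 with 20% dropout give 24/0.8 = 30, which matches the stated total. The 12 itself cannot be reproduced, because no effect size or SD is given. Solving backwards with the noncentral t, 12 per arm gives 80% power for a between-group difference in change of 0.757 baseline SD. That difference d is used below.

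**Per-subject variance and expected contrast for each test:**
- Raw change, or interaction: variance 2(1 − r) = 0.40; contrast d = 0.757. With two time points the interaction F is the square of the raw-change t, so these are one test.
- Group main effect: variance of the pre/post mean (1 + r)/2 = 0.90; contrast d/2 = 0.378.
- ANCOVA: variance 1 − r² = 0.36, times 1 + 1/(N − 4) = 1.05 at N = 24 for estimating the slope, giving 0.378; contrast d = 0.757.

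**Noncentrality = contrast / √(variance × 2/12), and power:**

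| Test | Noncentrality | df | Power |
|---|---|---|---|
| Group main effect | 0.378/√0.150 = 0.98 | 22 | about 15% |
| Interaction / raw change | 0.757/√0.0667 = 2.93 | 22 | 80% |
| ANCOVA | 0.757/√0.063 = 3.02 | 21 | 82% |

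Simulation with 40,000 trials agrees: 15.6%, 80.0% and 82.0%. By the normal approximation, 80% power needs 99 per arm for the main effect and 11 for raw change, a ninefold ratio: (0.90/0.40) × 2² = 9.

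**Error rate if either ANOVA test may count.** With equal SDs, the pre/post mean and the change are uncorrelated, so the two tests are independent under the null: 1 − 0.95² = 0.0975, about 10% per outcome. Simulation gives 9.9%, and each test alone stays near 5%.

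**How the ANCOVA gain depends on r.** The ANCOVA/change variance ratio at N = 24 is 0.378/0.40 = 0.945 at r = 0.8, so 5.5% lower. At r = 0.9 it is 0.9975, no gain. At an assumed r = 0.5 it is 0.7875; for the same 0.757 SD difference, power is 43% for change and 51% for ANCOVA, about 9 points.

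**Chance imbalance.** With 12 per arm, a baseline difference above 0.5 SD in either direction has probability 2(1 − Φ(0.5/√(2/12))) = 0.22. Given an imbalance of 0.5 SD, the change score is off by −(1 − r) × 0.5 = −0.10 SD at r = 0.8 and −0.25 SD at r = 0.5. In simulation ANCOVA was off by no more than about 0.01 and 0.02 SD.

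**Percentage change.** At r = 0.8 and an assumed baseline coefficient of variation of 15%, simulated power is 76%, against 80% for raw change; at an assumed 30% it is 63%. The protocol gives no coefficient of variation, so the size of this loss is illustrative.

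**The case against.** The strongest reply is that the plan already contains a correct comparison. The sentence that names the main effect also names the time-by-group interaction, which is unbiased under randomisation, holds a 5% error rate and uses each subject's baseline. Reporting every ANOVA term is conventional, and nothing makes the main effect the basis of the conclusion. This stands: a reader might infer that the trial has no valid between-group test or throws baseline information away, and the protocol does not support that. At r = 0.8 the change score already cuts the variance from 1.00 (post value alone) to 0.40, against 0.36 for ANCOVA in large samples.

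A reader might also infer that change scores are biased and that ANCOVA is free. Both methods are unbiased over randomisations and differ only given a chance imbalance. ANCOVA spends one degree of freedom and must estimate a slope. At the protocol's own r it gains about 2 points. Larger gains need a lower correlation, which the protocol does not document for any outcome.

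Nor does the main-effect test, taken alone, produce excess false positives; its fault is the wrong contrast and low power. The 10% arises only if either ANOVA result may count.

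Finally, the first hypothesis, that both arms improve, is addressed by the paired t-tests, and covariate adjustment is often left to an analysis plan, which is not at hand. That weakens the case for requiring ANCOVA. It does not justify the main-effect test, which the protocol itself specifies, or the lack of a deciding test among those it lists.

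**Conclusion.** The point holds for outcomes with one pre and one post value. The group main effect is the wrong contrast there: it carries half the training difference and has about 15% power where the interaction has 80%. Leaving the tests unranked allows about 10% type I error per outcome if either the main effect or the interaction may count. Baseline-adjusted ANCOVA is the better single test, by a small margin at r = 0.8, none at r = 0.9 and about 9 points at an assumed r = 0.5, and it protects against chance imbalance in a trial this small.

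These figures rest on the assumptions listed with the calculation. The point does not extend to PAES: with every score taken during the training period, a group effect across sessions remains an appropriate contrast. Severity is moderate, and the change is a cheap improvement; the planned interaction test remains valid.

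**What to change.** In the Statistical analysis section, for VO2max, body composition, lipids and sex hormones:

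1. Name one between-group test per outcome: ANCOVA of the post-training value on group with the baseline value as covariate, reporting the adjusted difference and its 95% confidence interval.
2. State that the ANOVA group main effect is not used as evidence of a training difference for these outcomes.
3. Keep percentage change as a descriptive column without a test.
4. State separately that PAES is compared between groups across sessions, without a baseline covariate.

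The cost is one paragraph of wording and one degree of freedom per outcome. No new data are needed.

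### Hypothesis 1 claims that each programme causes improvement, but its only listed tests are paired t-tests within two exercising arms, which cannot separate training from other pre/post change

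*Protocol*

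**What the plan says.** The hypotheses close the Background of the Project section. The first is that "both HIIT and MVCT would induce improvements in cardio-metabolic parameters"; the outcomes it lists are VO2max, weight, fat, lipids and sex hormones. The Objectives section puts the aim differently: "the purpose of this study was to compare the effects of 5-week HIIT and MVCT interventions".

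On design, the Participants section states: "The subjects will be randomly assigned to either HIIT or MVCT group". There is no non-exercise arm.

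The Statistical analysis section lists three sets of tests on pre/post data:

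- a mixed ANOVA "to test the main effect (i.e., group effect) and the interaction effect (time and group interaction) on the outcome variables";
- a paired t-test in each arm, whose purpose is given in these words: "For within-group change from pre- and post-values of the relevant outcome variables of interest";
- an independent-sample t-test "to determine the differences of the change and of the percentage change between the two groups".

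The ANOVA sentence names the group effect and the interaction but not the time effect. The paired t-tests are therefore the only listed tests that address hypothesis 1.

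**The concern.** The hypothesis is causal and is made for each programme separately. Randomisation protects the contrast between HIIT and MVCT. It does not protect the change within either arm, because nobody is observed over the same interval without training.

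The protocol itself leaves room for change that is not due to training:

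- **Test familiarity.** The VO2max section describes one graded test at each time point and no practice test.
- **Cycle phase.** The Experimental protocol section allows testing in either of two menstrual phases and does not require the same phase at both visits. Estradiol and testosterone are outcomes.
- **Diet and daily activity.** Participants are asked to keep both unchanged. Diet recall includes a pre-intervention week, but pedometers are worn only during the training weeks, so a change in activity from baseline would not be seen.
- **Regression to the mean.** Women enter on body fat above 30%. This matters only if the screening reading also serves as the baseline value, which the protocol does not say.

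At stake is what the trial may conclude. Significant paired tests in both arms would appear to confirm that each programme works, although neither randomisation nor a control supports that conclusion.

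**Working it through.** **Inputs from the protocol (Participants section).** Power 0.80, alpha 0.05, pre/post correlation r = 0.8, 12 in the HIIT group, 20% dropout, total 30.

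**Assumptions.** Two-sided tests, 1:1 allocation, 12 completers in the MVCT arm too, equal SD before and after, and normally distributed changes.

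**Step 1: the plan's own total.** 12 / (1 − 0.20) = 15 per arm, and 2 × 15 = 30. This reproduces. The 12 itself cannot be reproduced, because no effect size or SD is given. If it came from a paired t-test, it implies a mean change of 0.89 SD of change.

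**Step 2: SD of change.** In baseline SD units, sqrt(2 × (1 − 0.8)) = sqrt(0.4) = 0.632. The 0.89 in step 1 is therefore 0.89 × 0.632 = 0.56 baseline SD.

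**Step 3: paired test under drift alone.** Suppose training does nothing and both arms drift by d baseline SD in the favourable direction. The paired t statistic then has 11 degrees of freedom and noncentrality (d / 0.632) × sqrt(12). The critical value is 2.201. The chance of a significant favourable change in a given arm is:

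| Assumed drift (baseline SD) | Noncentrality | Paired test significant |
|---|---|---|
| 0.1 | 0.55 | 7% |
| 0.2 | 1.10 | 17% |
| 0.3 | 1.64 | 32% |
| 0.4 | 2.19 | 52% |
| 0.5 | 2.74 | 70% |

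The nominal two-sided rate is 5%. The table counts only significance in the direction of the drift. The opposite tail adds less than 1 percentage point at 0.1 and about 0.1 point at 0.2.

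**Step 4: the randomised contrast under the same drift.** A common drift cancels in the difference between arms. In simulation with 12 per arm, the planned independent t-test on change rejected in about 5% of trials at every drift in the table.

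**Step 5: would the time effect rescue the hypothesis?** No. The ANOVA time effect pools the same uncontrolled pre/post change over both arms, so naming it would leave the attribution problem as it is.

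**The case against.** The strongest reply is that the trial is comparative. Its stated purpose is to compare the two programmes, which needs no non-exercise arm, and the Statistical analysis section already tests that comparison directly, by the interaction and by a t-test on change. This stands, and it is why neither a control arm nor a change of test is asked for. It does not cover hypothesis 1, which is a separate claim about each programme.

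The protocol also takes some precautions: instructions to keep diet and activity normal, diet recall, pedometers, testing scheduled by cycle phase, and the same encouragement from the same helpers. These may reduce drift. They do not measure what would have happened without training.

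Regression to the mean is the weakest of the listed sources. Baseline measures are described as taken 3 to 7 days before training. If body fat is measured afresh then, most of the selection effect has already passed. The cut-off also does not select directly on VO2max, lipids or hormones.

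Two stronger readings are tempting, and the protocol supports neither.

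- A reader might infer that the arms will be compared by their separate paired p-values. With identical true effects and 80% power per arm, exactly one arm would be significant in 2 × 0.8 × 0.2 = 32% of trials. But no sentence plans such a comparison, and the direct between-arm tests are specified.
- A reader might infer that a non-significant difference will be reported as similarity. With 12 per arm, the 95% CI half-width of 0.85 SD of change would be too wide for that. But no hypothesis or objective claims equivalence. The mention in the Abstract of effects similar to or better than endurance training describes existing evidence.

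Both figures describe possible misuse of the results, not an error in the plan.

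**Conclusion.** The point holds for attribution only. Hypothesis 1 is worded causally for each arm, both arms exercise, and the only listed tests of it are within-arm paired t-tests. The plan as written would therefore support a training-effect conclusion that the design does not protect.

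The size depends on a drift that the protocol does not give. For an assumed drift of 0.2 to 0.4 baseline SD with no training effect, 12 per arm and r = 0.8, the false-positive rate is about 17% to 52% per arm instead of 5%. At 0.1 baseline SD the excess is small. The drift may also differ between outcomes: test familiarity bears on VO2max and cycle phase on the hormones.

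The planned between-arm tests are sound on this point, since they are unaffected by drift common to both arms.

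**What to change.** Three changes of wording:

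1. In the hypotheses, state hypothesis 1 as improvement from baseline in each arm. Keep the direction and drop the causal verb *induce*.
2. In the Statistical analysis section, present within-arm mean changes with 95% CIs as descriptive.
3. In the same section, state that conclusions about programme effects rest on the randomised contrast already planned, either the time-by-group interaction or the between-arm difference in change, with its 95% CI.

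The cost is a more modest claim: the trial could say how the programmes differ and how values moved in each arm, but not that each programme caused its own change. The total stays at 30, no arm is added, and the planned between-arm tests are unchanged.
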